#### Quality of life assessment

Quality of life (QoL) will be assessed at baseline and every six months thereafter by administration of the KDQOL-SF™ 1.3 questionnaire. This self-administered tool includes 2 QoL instruments, the SF36 and the KDQOL, which are generic and CKD-specific QoL measures, respectively. The KDQOL-SF™ 1.3 questionnaire consists of 18 scales: 8 from the SF-36 questionnaire [13,14] (physical function, role limitations caused by physical health problems, role limitations caused by emotional health problems, bodily pain, general health perception, vitality, social activities, and mental health) and 10 from the KDQOL questionnaire [15] (symptoms, effects of kidney disease on daily life, work status, cognitive function, quality of social interaction, sexual function, sleep, social support, patient satisfaction).

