#### Clinical feasibility assessment and cost-efficacy analysis

The clinical feasibility of the two therapeutic strategies will be assessed by reviewing the following: number of patients in each arm who maintain stable Hb levels between 10.0 and 12 g/dL, without need for > 50% change in the allocated dose of ESA; number of ESA dose variations from time of randomization to time of Hb level stabilization (between 10.0-12.0 g/dL); average variation of allocated ESA dose (IU/week for erythropoietins or microgram/week for darbepoetin) in the two arms; average ESA dose variation based on weight and body mass index; time from randomization to the first ESA dose variation; time from randomization to Hb level stabilization (between 10.0-12.0 g/dL); number of blood transfusions and number of patients requiring one or more blood transfusion.

In addition the cumulative in-centre and out-centre costs of managing dialysis patients allocated to the high versus low fixed ESA doses will be assessed in a subset of the overall population.

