#### Data analysis

Analysis will be by the intention-to-treat principle. The incidence rate of events in the high dose versus the low dose ESA groups will be estimated using Kaplan-Meier curves. Log-rank test will be used to compare the two curves [17].

Additional multivariate analyses will be performed using a Cox proportional hazards model [17]. The proportional hazards assumption will be checked by graphical inspection of log (-log [survival]) plot. Analyses will be performed for assessment of the efficacy of study interventions (high doses or low doses of ESA) on any of the end-points of this study, including quality of life and costs. The treatment effect on outcomes, quality of life, and costs will be also evaluated through subgroup-analysis based upon a series of potential effect modifiers (baseline information) including socio-demographic factors (gender, age, ethnicity, marital status, education, occupational status), presence or absence of cardiovascular risk factors (diabetes mellitus, hypertension, cigarette smoking, family history of cardiovascular disease), presence or absence of previous major cardiovascular event, presence or absence of other major concomitant illness, type of ESA administered, average ESA dose administered during the study, metabolic control (quartiles of total/LDL/HDL-cholesterol and HbA1c), other cointerventions (iron, vitamin D or vitamin D analogues, phosphate binders, calcimimetics, antihypertensive agents, statins, anticoagulants), baseline and end of treatment levels of calcium, phosphorus, iron, parathyroid hormone; Kt/V, dry weight, dialysis blood flow rate, interdialytic weight gain, type of dialysis (bicarbonate-dialysis, high versus low flux, hemodiafiltration, online hemodiafiltration, hemofiltration, acetate-free biofiltration), dialysis duration (minutes per dialysis session) and dialysis vintage (months). Existing trends in the efficacy based upon these subgroup analyses will be tested with the Mantel-Haenszel test for each of these covariates. A chi-square test will be used to assess heterogeneity of observed effects of interventions.

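### The protocol tests quality-of-life and cost subgroup effects with Mantel-Haenszel, which suits neither repeated KDQOL-SF scores nor cumulative costs

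*Protocol article*

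**What the plan says.** All of the named methods stand in the Data analysis section of the protocol article.

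- Events: "The incidence rate of events in the high dose versus the low dose ESA groups will be estimated using Kaplan-Meier curves", and "Log-rank test will be used to compare the two curves".
- Modelling: "Additional multivariate analyses will be performed using a Cox proportional hazards model", followed by a graphical check of proportional hazards.
- Scope: analyses are to be done "on any of the end-points of this study, including quality of life and costs". This sentence names no method.
- Subgroups: "The treatment effect on outcomes, quality of life, and costs will be also evaluated through subgroup-analysis", over a long list of covariates.
- Test for those subgroups: "Existing trends in the efficacy based upon these subgroup analyses will be tested with the Mantel-Haenszel test for each of these covariates". A chi-square test for heterogeneity of effects follows.

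The data in question are described elsewhere in the article. Under Quality of life assessment: "Quality of life (QoL) will be assessed at baseline and every six months thereafter", with the KDQOL-SF. Under Clinical feasibility assessment and cost-efficacy analysis, cumulative costs by arm "will be assessed in a subset of the overall population". Aims 2 and 4 are the effect on quality of life and a cost-effectiveness analysis.

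**The concern.** The subgroup sentence includes quality of life and costs, and the next sentence refers back to those same analyses and gives them one test. That test belongs to stratified tables of events. KDQOL-SF scales are numeric scores measured repeatedly, with a baseline value. Cumulative cost is a numeric total built up over follow-up of unequal length. This is therefore a stated method attached to outcomes it does not suit, and not merely a detail left for later.

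Two of the four stated aims are at stake. An analysis plan that followed the text would inherit the mismatch. One that departed from it would contradict the published protocol. Either way, the subgroup results for quality of life and costs would lack the natural estimate, a difference in means with its confidence interval.

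**Working it through.** **1. The plan's own figures.** The article gives no standard deviation, target difference, correlation or power for quality of life or costs, so there is no figure on this point to reproduce. Its event target does reproduce. With hazard ratio 0.85, 80% power and alpha 0.05 (taken as two-sided), Freedman's formula gives (1.960 + 0.842)² × (1.85/0.15)² = 7.849 × 152.1 = 1194. That target concerns the primary endpoint only and plays no part below.

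**2. Which method reaches which outcome.**

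| Method | What the text ties it to | Does it reach quality of life and costs? |
|---|---|---|
| Kaplan-Meier, log-rank | Incidence of events | No |
| Cox | Additional multivariate analyses | Not stated; only suggested by the order of the sentences |
| Mantel-Haenszel | The subgroup analyses just described | Yes; those analyses expressly include both |
| Chi-square | Heterogeneity of effects | Yes, but it can be computed from subgroup mean differences |

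The Mantel-Haenszel sentence speaks of trends in efficacy. That word does not restrict it to clinical events, because the Study Outcomes section lists quality of life and costs among the outcomes by which efficacy is compared.

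**3. Shape of the data.** Recruitment is expected to take 12 months, and follow-up to end about 4 years after the last enrolment. Planned observation therefore runs from about 4 to about 5 years. At one questionnaire every six months, that is 4/0.5 = 8 to 5/0.5 = 10 scores per scale after baseline, for a patient who stays under observation. Observation time for costs differs by up to about a year through staggered entry alone, before deaths and the assumed 5% dropout are counted.

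**4. Fit.** In stratified-table form, Mantel-Haenszel takes one classified result per patient. To use it, 8 to 10 scores must become one category, or one visit must be picked. A cost total must be cut into bands. The result is a test of association or a pooled ratio, not a difference in mean score or mean cost.

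**5. What a baseline-adjusted model can offer (illustration).** Let ρ be the correlation between baseline and follow-up score, which is an assumption because the article gives none. For a single follow-up score with variance set to 1:

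- Follow-up score alone: 1
- Change score: 2(1 − ρ)
- Adjusted for baseline: 1 − ρ²

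| ρ (assumed) | Adjusted variance | Reduction against follow-up alone, ρ² | Reduction against change score, 1 − (1 + ρ)/2 |
|---|---|---|---|
| 0.5 | 0.75 | 25% | 25% |
| 0.6 | 0.64 | 36% | 20% |
| 0.7 | 0.51 | 49% | 15% |

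The article proposes neither comparator. The table shows what the baseline score is worth, not a loss under the stated plan.

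**The case against.** The strongest case against is that this is a condensed article. A longitudinal model, baseline adjustment and the handling of incomplete costs are commonly left to the full protocol or analysis plan, neither of which is shown. That stands: their absence alone is no finding. It does not cover the Mantel-Haenszel sentence, which names a test and attaches it to these outcomes.

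It can also be said that extended Mantel-Haenszel statistics accept numeric scores without cutting them, and that the talk of trends is compatible with such a version. This is true, and it is why the point is confined to the usual stratified-table form. Even the extended version takes one value per patient, ignores the repeated measurements and gives no mean difference. The chi-square heterogeneity test can work on mean differences and needs no criticism.

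A reader might go further in three ways, none of which the document supports:

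- *Quality of life and costs are to be analysed by log-rank or Cox.* Kaplan-Meier and log-rank are tied to events, and the sentence that widens the scope names no method. Cox regression on a cost scale is proposed nowhere, so the bias it could bring has no target here.
- *The baseline score will be discarded.* The article does not say how the baseline score will be used. That is silence, not a decision to leave it out.
- *Precision will be lost by dichotomising.* A median split of a normal score keeps 2/π = 64% of the information, but no median split is planned.

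**Conclusion.** The point holds in a limited form. The protocol attaches Mantel-Haenszel to subgroup analyses that expressly include quality of life and costs. In its usual form the test suits neither outcome, and it cannot supply the mean differences that aims 2 and 4 need. The remaining methods named for estimating or comparing arms are for events, so the text offers no fitting alternative.

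No trial-specific loss can be computed. The variance reduction of 25% to 49% from baseline adjustment rests on an assumed correlation of 0.5 to 0.7 and is measured against follow-up scores alone. The primary composite and its analysis are not affected. The correction is worth making because it touches two of the four aims and costs little.

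**What to change.** - **Mantel-Haenszel sentence:** limit it to event outcomes.
- **KDQOL-SF scores:** for each scale, use a repeated-measures model with arm, visit and arm-by-visit, adjusted for the baseline score and for centre (the stratification factor). Report adjusted mean differences with 95% confidence intervals. Test subgroups as treatment-by-covariate interactions in that model.
- **Scores after death:** state how they are handled. Death is part of the composite, and a repeated-measures model otherwise treats the missing scores implicitly as if they could have been observed.
- **Costs:** report the difference in arithmetic mean cost with a bootstrap confidence interval. Allow for unequal follow-up, for instance by inverse-probability-of-censoring weights.

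The cost is a few lines of wording, a little more analysis work and one decision on scores after death. No further data are needed: the baseline and six-monthly questionnaires and the costs are already to be collected.

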Taken together, these data showing increased harm and limited evidence for benefit bring anemia management in chronic kidney disease back to its origins. Initially, ESA were introduced to treat anemia in patients with ESKD receiving hemodialysis for renal replacement therapy, and who required red blood cell transfusions to elevate severely reduced hemoglobin levels. Given this identified benefit of ESA treatment, namely a significant reduction in the rate of transfusion [8], the question of potential treatment efficacy was expanded and explored in the pre-dialysis setting where subsequently no beneficial effects and the potential for harm have been clearly demonstrated. In light of the absence of benefit from targeting hemoglobin levels for patients with CKD, it is now important to understand whether alternative therapeutic strategies to manage anaemia in CKD can be found and whether a fixed dose ESA strategy (high or low) might increase hemoglobin levels without signifcant harm (adverse vascular events and mortality).

The mechanism by which targeting Hb levels above 12.5 g/dL causes an increase in the risk of death and cardiovascular events remains uncertain. It is possible that the ESA dose required to achieve and maintain higher Hb targets is directly linked with adverse events, most particularly in patients who are resistant to the actions of administered ESA [9,10]. Further, evaluating differing fixed doses of ESA is difficult because Hb levels inextricably link to ESA dose and demonstrably affect patient outcomes.

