### Study design

This will be a pragmatic, multicenter, centrally randomized, controlled trial (Figure 1) based upon the intention-to-treat principle. To achieve allocation concealment, randomization will be carried out centrally by the coordinating study center. Independent of baseline Hb level, participants will be allocated to ESA 4000 IU/week intravenously versus 18000 IU/week intravenously of erythropoietin alfa, beta, or equivalent doses of any other commercially available agent (including darbepoetin alfa, C.E.R.A. or biosimilars and other agents, which may become available). Randomization will be stratified by enrolling center and treatments will be assigned by random permuted blocks of six patients.

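### The subgroup list is labelled baseline but includes average ESA dose during the study and end-of-treatment laboratory levels; arm comparisons within such groups are not protected by randomization

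*Protocol article*

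**What the plan says.** All the subgroup text is in the protocol article, Statistical methods, Data analysis.

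- **Purpose:** "The treatment effect on outcomes, quality of life, and costs will be also evaluated through subgroup-analysis".
- **Label given to the variables:** "a series of potential effect modifiers (baseline information" (the parenthesis closes directly after these words).
- **Entries that cannot be baseline:** the middle item of "type of ESA administered, average ESA dose administered during the study, metabolic control", and the second half of "baseline and end of treatment levels of calcium, phosphorus, iron, parathyroid hormone".
- **Tests:** "Existing trends in the efficacy based upon these subgroup analyses will be tested with the Mantel-Haenszel test for each of these covariates". A chi-square test for heterogeneity is added.

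No caution, adjustment or exploratory label is attached to the two entries, and no other section corrects them.

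Three other sections bear on average dose. Study design makes dose the randomized factor: "participants will be allocated to ESA 4000 IU/week intravenously versus 18000 IU/week intravenously of erythropoietin alfa, beta". The same section moves the dose by 25% at a time whenever Hb leaves 9.5-12.5 g/dL. The clinical feasibility section counts variation of the allocated dose in each arm among its outcomes.

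**The concern.** A subgroup comparison keeps the protection of randomization only if membership is settled before allocation. Average dose during the study is set by the arm, by the patient's Hb response, and by how long the patient stays alive and under observation. The document itself treats dose variation as an outcome in one section and as a baseline modifier in another.

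Hb response may also be prognostic. The Background raises the possibility that dose-related harm falls "most particularly in patients who are resistant to the actions of administered ESA". If so, arms compared within a dose stratum differ in prognosis before any treatment effect is counted.

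At stake are the secondary results. A table of arm effects by delivered dose, with a formal trend test, could show a strong gradient when none exists. End-of-treatment laboratory levels can also respond to treatment and to survival, so the principle is the same, though they do not encode the arm as average dose does.

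**Working it through.** **1. The plan's own figure.** The document gives no number for the subgroups, so the design effect serves as the yardstick. With hazard ratio 0.85, 80% power and alpha 0.05 (taken as two-sided), Freedman's formula gives (1.960 + 0.842)² × (1.85/0.15)² = 7.849 × 152.1 = 1194 events, exactly the target in Study design. The trial is sized to detect 0.85.

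**2. Who crosses between dose groups.** If each step is 25% of the current dose:

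- Low arm, upward: 4000 → 5000 → 6250 → 7813 → 9766 IU/week.
- High arm, downward: 18000 → 13500 → 10125 → 7594 IU/week.

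The pooled median average dose in the simulations below was 7,893 to 8,586 IU/week. For the prescribed dose to pass it, a low-arm patient needs four increases and a high-arm patient three decreases. The crossers are therefore selected on response, and they must stay in the study long enough to be titrated.

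**3. Simulation with no treatment effect.** 300,000 patients per scenario.

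- *From the document:* 1:1 allocation to 4000 or 18000 IU/week, 25% steps outside 9.5-12.5 g/dL, visits at months 1, 2, 3 and then every 6 months, event rate 15% a year (used as a hazard of 0.15), 4-5 years of follow-up.
- *Assumed:* a latent resistance score shifts Hb by 1 g/dL per SD; Hb rises 0.5 or 1.0 g/dL per dose doubling; mean Hb 11 at 9000 IU/week; Hb noise SD 0.4; event hazard multiplied by 1.0, 1.25 or 1.5 per SD of resistance; titration only at the scheduled visits.

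The overall low/high rate ratio was 0.997-0.998, as it should be. Split at the pooled median of average dose:

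| Hazard ratio per SD of resistance | Hb rise per doubling (g/dL) | Lower-dose half | Upper-dose half |
|---|---|---|---|
| 1.0 | 0.5 | 1.94 | 0.47 |
| 1.0 | 1.0 | 1.97 | 0.45 |
| 1.25 | 0.5 | 2.96 | 0.69 |
| 1.25 | 1.0 | 2.90 | 0.62 |
| 1.5 | 0.5 | 4.19 | 0.90 |
| 1.5 | 1.0 | 3.96 | 0.79 |

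The ratios are false even when resistance carries no risk, because crossing takes time in the study. When resistance does carry risk, the two biases add in the lower half (its high-arm patients are long-stayers and good responders) and offset in the upper half (its low-arm patients are long-stayers but poor responders).

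**4. Would the planned tests notice?** Scaled to 2204 patients, the first row has 511 low-arm and 30 high-arm events in the lower half, and 27 and 512 in the upper half. The standard errors of the log rate ratios are √(1/511 + 1/30) = 0.188 and √(1/27 + 1/512) = 0.197. The difference between halves is (0.663 + 0.755)/√(0.188² + 0.197²) = 5.2 standard errors, a heterogeneity chi-square of about 27 on 1 df. Across the six rows the same calculation gives 4.8 to 6.2 standard errors.

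**5. Other cuts.** Per 2204 patients, the lowest tertile holds 713-728 low-arm against 7-22 high-arm patients, and the highest 2-14 against 722-739. These barely contain a comparison. The middle tertile gave 1.00-1.03, about 1.6 and about 2.3 at hazard ratios 1.0, 1.25 and 1.5 per SD. A fixed band of 6000-14000 IU/week gave 0.89 to 2.28.

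**6. Check of the remedy.** Tertiles of baseline resistance, in the same simulated data, gave 0.995 to 1.002 in every scenario.

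**7. Sensitivity.** A separate null simulation used other assumptions: Hb 11.5 at 13,944 IU/week, 1.0-1.5 g/dL per doubling, hazard ratio 1.2-1.5 per SD. It gave 1.9-3.0 in the lower half and 0.45-0.85 in the upper half.

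**The case against.** **Little of the trial depends on this.** The primary analysis is intention-to-treat with Kaplan-Meier curves and a log-rank test, the interim criterion concerns the primary endpoint, and neither sample size nor event target uses a subgroup. This stands and limits the severity. A reader might infer that the main result is compromised; nothing in the document supports that. Nor does it give the average-dose subgroup the role of answering the dose question. The first aim is the comparison of the two allocated doses, which the randomized contrast answers.

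**The numbers are not predictions.** The Hb slope, the spread of resistance, its risk and the cut points are not in the document, and Study design sets no Hb-check interval. This also stands. The two halves of a median split erred in the same directions in every scenario, but the sizes vary, and in a fixed middle band even the direction varies.

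**The laboratory levels are different.** Both arms are managed toward the same calcium, phosphorus and PTH targets, and these values do not encode the arm. Large false effects should not be inferred for them; they were not simulated. They are still post-randomization under a baseline label.

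**Other entries may be sound.** ESA type and co-interventions can be read as baseline, so they are not counted as errors. A reader might also call the absence of baseline Hb or ESA resistance a defect. It is not one: the list is open-ended, the article is condensed, the Background names resistance only within a possible mechanism, and patients new to ESA have no prior dose.

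None of this removes the contradiction between the label and the two entries.

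**Conclusion.** The point holds as a should-fix for the secondary analyses. The sentence contradicts itself, and for average delivered dose the planned arm comparison is biased by construction, since the stratifier is the randomized treatment modified by response and by time in the study. Under the stated assumptions the false rate ratios after a median split are about 1.9 to 4.2 and 0.45 to 0.90. Most lie further from 1 than the design effect of 0.85, and the heterogeneity they create would be clearly significant at the planned trial size. The presence of bias follows from the design; its size depends on parameters the document does not give. For end-of-treatment laboratory levels only the principle is established.

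**What to change.** In Data analysis:

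1. State that effect-modifier subgroups use only values recorded at or before randomization.
2. Remove average delivered ESA dose and the end-of-treatment levels from the list, keeping the baseline levels.
3. State that ESA type and co-interventions are those in use at baseline.
4. If delivered dose or end-of-treatment values are to be studied, place them in a separate analysis labelled exploratory and non-randomized, either descriptive or by a method that allows for time-varying confounding.

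Adding baseline Hb or prior ESA dose as modifiers is optional; for prior dose, say how patients new to ESA are handled. The planned heterogeneity test can stay. Interaction terms in the Cox model would be a preference, not a correction.

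The cost is wording only. No dose, visit, event target or sample size changes. The edit should be made before outcome data are analyzed by arm.
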